**2.2** **Secondary objectives**

- Compare the number and severity of rejection episodes in the pancreas allograft to the ones occurring in the kidney allograft (SPK), and the ones diagnosed by the duodenal segment biopsies.
- Compare pancreas graft survival at 12, 36 and 60 months after transplantation between the prospective study group and retrospective control group.
- Monitor kidney (and pancreas) graft survival (SPK) 12, 36 and 60 months post-Tx.
- Compare patient survival at 12, 36 and 60 months post-Tx.
- Compare the incidence of non-surgical complications (infections,cardial complications, pulmonary complications and neurological complications).
- Explore if potentially graft devastating complications in pancreas transplants can be detected earlier with the microdialysis method than by current standard of care
- Explore if new complication specific biomarkers can be detected by the microdialysis method

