**2.3 Immunological studies**

- Scheduled endoscopic (EUS) biopsies will be taken according to our present routine protocol; simultaneously from these four transplant/organ sources at predestined points of time:

- Pancreas transplant (*P*)

- Kidney transplant (*K*)

- Duodenal segment of pancreas transplant (*tD*)

- Duodenum of recipient = native Duodenum (*nD*) – Serves as ‘control’

• Baseline (Day 0; at Tx): *K +tD + nD* - These will be taken during surgery

• 3 weeks post-Tx: *P +tD + nD* - Endoscopic

• 6 weeks post-Tx: *P + K + tD + nD* - Endoscopic (P/tD/nD) + Percutaneous (K)

• 12 months post-Tx: *P + K + tD + nD* - Endoscopic (P/tD/nD) + Percutaneous (K)

Within the study, we also want to take conventional percutaneous, ultrasound-guided P biopsies at 6 weeks and 12 months post-Tx – in order to compare the yield (and complications) by EUS vs percutaneous P biopsies.

In addition, indication biopsies will be taken whenever there is suspicion of rejection

in either organ. Preferably, simultaneous P + tD + nD endoscopic biopsies, P

percutaneous biopsies and K percutaneous biopsies should be obtained.

All biopsies will be examined at our local pathology unit; the pancreas and duodenal biopsies by prof. [name] and dr. [name]; the kidney biopsies by prof. [name] and dr. [name]. The pancreas and kidney biopsies will be evaluated by well-known BANFF criteria, while duodenal biopsies will be rated according to Wu et al. (27).

- Histological evaluation of the scheduled and indication biopsies will involve comparisons between biopsies from the various transplants/organs of the same patient.
  - Rejection histology scores.
  - Immunoshistochemistry on immunologic markers (CD25, FOXP3, CD4, CD3, CD8, CD45RO, perforin, granzyme A/B, etc).
    - Blood samples will be obtained at the time of transplantation and the later scheduled appointments indicated above.
  - Study of immune cell activation (CD25, FOXP3, CD4, CD3, CD8, CD45RO, perforin, granzyme A/B, etc) and cytokines (IL-2, TNF-a, IFN-g, IL-10, IL-12 etc).
  - Compare biomarkers in serum, indicative of acute rejection, by at least weekly blood sampling post-Tx (RNA microarray on a series of genes related to rejection, quantitative PCR on selected genes) (28-29).
  - Study of donor specific antigens (DSA)
    - DSA present pre-Tx (already routine)

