**2.7 Pancreas transplant monitoring with microdialysis catheters**

- At end of surgery totally three microdialysis catheters will be inserted. The catheters membranes have a 100 kDa pore size, an outer diameter of 0.6 mm and a length of 30 mm. A secure thread is positioned 60 mm from the tip (CMA 65, CMA Microdialysis AB, Stockholm, Sweden).The left abdominal wall will be punctured at three different locations close to each other by a hypodermic needle (Sterican® 14G X 3 1/8 “, B. Braun AG, Melsungen, Germany) through which the microdialysis catheter will be led. After removing the hypodermic needle one microdialysis catheter will be sutured to superfluous connective tissue on the pancreas graft, one will be sutured to the fascia of the right psoas muscle implying that the pancreas graft will be in direct contact with the catheter, and one catheter will be secured close to the duodenoduodenostomy. The catheters will be secured to the skin using a 4.0 thread. Each catheter will be perfused with 6 % hydroxyethyl starch at a rate of 1 µL/minute by microinjection pumps (CMA 107, CMA Microdialysis AB, Stockholm, Sweden), and the samples will be collected in microvials (CMA Microdialysis AB, Stockholm, Sweden)
- Postoperatively the microdialysis samples will be analyzed every second hour at the bedside for glycerol, glucose, lactate, and pyruvate using a microdialysis analyzer (Iscus Flex, CMA Microdialysis AB, Stockholm, Sweden).The lactate to pyruvate ratio will be calculated. Thereafter the samples will be frozen to -20°C and later to -80°C.
- Since this study is the first of its kind and threshold values for detecting e.g. pancreatic graft ischemia, leakages, and rejections have not been established we will not implement e.g. a decision tree in the protocol. However, since not only the physicians responsible for the studies, but also the nurses at ward have substantial experience with the microdialysis method, we expect that deviations from the normal course may lead to prescription of e.g. ultrasound Doppler examinations, and that graft complications thereby may be detected earlier. From a purely scientific point of view one could argue that blinding nurses and physicians for the results would be appropriate. However, we consider this not feasible since the researchers also are responsible for treating the patients and it is important that they have immediate access to the data to reveal e.g. inappropriate sampling.

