- The catheters will be left in situ for as long as they are able to sample appropriately, or until the patient is dismissed. The patient may at any time point request removal of the catheters. In our liver studies the patients had well-functioning catheters for a median of 10 days. The catheters are easily pulled out after loosen the skin secure. According to our experience from the liver- and Whipple studies removing the catheters is not associated with any risk or pain. After study completion the samples will be thawed and analyzed en bloc for a wide range of inflammatory mediators including complement factor 5 a and the chemokine CXCL-10, which were specific biomarkers for ischemia and rejection respectively in our previous liver study. These analyses will be performed in [name] lab in the Department of Immunology at our hospital. We will also consider analyzing samples for presence of various micro-RNAs.

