**10.3 Statistical methods in data analysis**

- The primary evaluation criteria ‘Incidence of rejection’ and ‘Rate of surgical complications’ will be evaluated for several populations:

- All patients who receive at least one dose of study medication, defined as the ‘Intention-to-Treat’ population.

- All patients who complete 12 months of intended study medication, defined as the ‘Intention completed’ population.

The analysis of these categorical parameters will consist of:

1. Comparisons of groups using the Fisher exact test.

2. Confidence intervals of 95% of the percentage of incidence of these

events.

- The loss of grafts and deaths will be analysed by the Kaplan-Meier method for estimating the time to events.
- Continuous (non-categorical) variables will be analyzed by student t-tests and chi-square tests.
- Microdialysis data are typically non-normally distributed. We will therefore use the Wilcoxon Signed rank test for repeated measurements and the Mann-Whitney U test for comparison of groups. We will also use linear mixed model analyses on log10 transformed data for repeated measurements. Receiver operating curves and contingency tables will be used to explore sensitivity and specificity.
- Any other methods that are not planned can be considered as alternative methods.

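### Open microdialysis readings can prompt the diagnoses they are judged against, so lead time is unobservable in prompted cases and accuracy for rejection carries verification bias

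*Protocol*

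**What the plan says.** **Aim and analysis.** Protocol Section 2.2 lists as a secondary objective: "Explore if potentially graft devastating complications in pancreas transplants can be detected earlier with the microdialysis method than by current standard of care". Section 10.3 adds: "Receiver operating curves and contingency tables will be used to explore sensitivity and specificity". It does not name the conditions to which this applies.

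**Use of the readings.** Under Section 2.7, samples from three catheters are analysed at the bedside every two hours. No decision tree is set, because "threshold values for detecting e.g. pancreatic graft ischemia, leakages, and rejections have not been established". The results are open to the ward: "we expect that deviations from the normal course may lead to prescription of e.g. ultrasound Doppler examinations", and "graft complications thereby may be detected earlier". The section grants that blinding would be preferable scientifically, then declines it: "However, we consider this not feasible since the researchers also are responsible for treating the patients". It adds that staff need the data at once to spot faulty sampling.

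**Catheter window.** Removal has no fixed day; catheters stay until they stop sampling properly or the patient goes home. The only duration given is: "In our liver studies the patients had well-functioning catheters for a median of 10 days". The flow chart (Section 15) marks microdialysis across the baseline, Day 4 and Day 10 columns and leaves it blank from Week 3.

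**Reference histology.** Section 2.3 schedules kidney, graft-duodenum and native-duodenum biopsies during surgery, without pancreas. The first scheduled pancreas biopsy is "3 weeks post-Tx: *P +tD + nD* - Endoscopic", followed by 6 weeks and 12 months. Otherwise biopsies are taken when rejection is suspected.

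**The concern.** A comparison of detection times needs two times per event: when microdialysis deviated, and when standard care would have found the problem. Here each patient has both, and the same clinicians act on both. Once a reading leads to a Doppler examination that finds the complication, the second time no longer exists. Section 2.7 describes this chain as the expected course, and nothing in the protocol records which diagnoses arose that way.

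An accuracy estimate needs a reference diagnosis whose availability does not depend on the test. For rejection that reference is histology. In the charted catheter window, pancreas histology is obtained only on suspicion, and visible readings can contribute to suspicion. Patients with positive readings may then be verified more often than those with negative readings.

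At stake is how the first pancreas data on this method will be read. A favourable ROC curve or a high share of early detections could partly reflect the workflow. A later analysis plan could not repair this, because the prompt for each work-up has to be noted when it happens.

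**Working it through.** The protocol gives no accuracy, power or sample-size figure for microdialysis, so there is no stated figure to reproduce. The check has three parts.

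**1. Timing of the reference standard**

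- Last charted microdialysis column: Day 10 (Section 15). Median catheter life in the liver studies: 10 days (Section 2.7).
- First scheduled post-transplant pancreas biopsy: 3 weeks, that is day 21 (Section 2.3).
- Gap: 21 − 10 = 11 days. None of the three scheduled pancreas biopsy times (3 weeks, 6 weeks, 12 months) lies in the charted window.
- The day 0 duodenal and kidney biopsies are taken during surgery, and the catheters go in at its end, so these biopsies cannot verify postoperative readings.

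Ten days is a median and removal has no fixed day, so some catheters could reach day 21. The distribution of catheter life is not given. Assumed range:

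- Lognormal with median 10: P(T > 21) = 1 − Φ(ln(2.1)/σ), which gives 0.7% for σ = 0.3, 6.9% for σ = 0.5 and 14.5% for σ = 0.7.
- Exponential with median 10: 2^(−2.1) = 23%.

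Discharge before day 21 would lower these figures. The overlap is a minority of catheters under every assumption tried.

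**2. Verification bias for rejection**

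Let v+ and v− be the probabilities that a patient with a positive or a negative reading receives a biopsy, and assume that biopsy depends only on the reading. Among verified patients:

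- apparent sensitivity = Se·v+ / [Se·v+ + (1 − Se)·v−]
- apparent specificity = Sp·v− / [Sp·v− + (1 − Sp)·v+]

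The documents give neither v+ nor v−. With v+ = 0.9 assumed throughout:

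| True Se / Sp | v− | Apparent Se | Apparent Sp |
|---|---|---|---|
| 0.50 / 0.50 | 0.6 | 0.45/(0.45+0.30) = 0.60 | 0.30/(0.30+0.45) = 0.40 |
| 0.50 / 0.50 | 0.3 | 0.45/(0.45+0.15) = 0.75 | 0.15/(0.15+0.45) = 0.25 |
| 0.60 / 0.80 | 0.6 | 0.54/(0.54+0.24) = 0.69 | 0.48/(0.48+0.18) = 0.73 |
| 0.60 / 0.80 | 0.3 | 0.54/(0.54+0.12) = 0.82 | 0.24/(0.24+0.18) = 0.57 |

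Under this model, apparent sensitivity rises and apparent specificity among verified patients falls whenever v+ exceeds v−. If v+ = v−, there is no bias.

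**3. Lead time**

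Let M be the first microdialysis deviation, S the time at which standard care alone would detect the event, and D the actual diagnosis.

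- If a standard sign comes first or arises independently, S can be dated and S − M can be computed.
- If the deviation prompts the work-up, D replaces S. When D falls between M and S, the measured interval D − M is shorter than the true lead S − M, yet the case is credited to microdialysis.

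The share credited to the test is thus inflated, while the measured interval may shrink. The net direction of the lead-time error cannot be derived from the documents.

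**The case against.** The strongest reply is that this is openly exploratory work. Both Section 2.2 and Section 10.3 speak of exploring, thresholds do not yet exist, and Section 2.7 discloses and explains the lack of blinding. A reader might infer that the protocol sets out to prove earlier detection; it does not. The choice of ROC targets and of a deviation rule could also sit in an analysis plan that is not shown. All of that stands. It does not cover the data collection: if the trigger for each work-up is not recorded, no later plan can separate prompted from unprompted diagnoses.

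Several stronger readings are tempting but unsupported:

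- **That standard-care detection is never observed.** Section 2.6 schedules daily blood sampling for the first 10 days and daily drain amylase until the drains are removed, whatever microdialysis shows. First standard signs can be dated for many events. Only microdialysis-prompted cases lose the comparator.
- **That every complication is affected equally.** The biopsy gap concerns rejection. Ischaemia and leakage are established by imaging, reoperation or drain fluid, and missed events would often surface clinically. Drain amylase partly protects leakage. Ischaemia has less protection, since Doppler is the examination that Section 2.7 names as prompted.
- **That the readings are known to drive biopsies.** Section 2.7 mentions examinations such as Doppler, not biopsy. That readings contribute to suspicion of rejection is plausible, but it is an inference.
- **That no catheter could overlap a scheduled pancreas biopsy.** This is true of the flow chart and of the median, not of every patient.
- **That the stored-sample biomarkers are equally compromised.** C5a and CXCL-10 are assayed together after study completion, so their results cannot trigger work-up. They still inherit reference diagnoses that bedside readings may have prompted.

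**Conclusion.** The concern holds in a limited form. For microdialysis-prompted diagnoses, the standard-care detection time cannot be observed and the event counts for the test. For rejection, the charted window closes 11 days before the first scheduled post-transplant pancreas biopsy. Sensitivity and specificity therefore cannot be estimated without verification bias, unless positive and negative readings happen to be verified equally often.

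The size is not known. With 90% of positive and 30% to 60% of negative readings verified, a true sensitivity of 0.50 appears as 0.75 to 0.60. These rates are assumptions, as is the premise that biopsy depends only on the reading. The result also rests on catheter life in pancreas recipients resembling the liver median.

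A reader might infer that lead time will be overstated. That does not follow, because prompting can also shorten the measured interval; for prompted cases lead time is simply not identifiable. The point affects an exploratory secondary objective and does not bear on the two primary comparisons. It is still worth correcting, because the missing information can only be captured prospectively.

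**What to change.** Keep the readings visible to staff and make three changes.

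1. **Record the prompt.** For each graft complication, enter in the CRF at the time what first prompted the work-up (microdialysis or a named standard sign) and the date and time of the first standard sign.
2. **Define lead time.** Measure it from the first microdialysis deviation to the first standard sign. Use one written deviation rule, applied to the stored two-hourly values without knowledge of outcome. Report microdialysis-prompted diagnoses separately as having no observable standard-care time.
3. **Restrict the accuracy claims.** Report microdialysis results for rejection descriptively only. For ischaemia and leakage, show ROC results with and without microdialysis-prompted diagnoses, and label them hypothesis-generating.

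The cost is two CRF items per complication and some protocol wording, with no new samples or biopsies. The downside is fewer events in each estimate and no rejection ROC for microdialysis.

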**2.3 Immunological studies**

- Scheduled endoscopic (EUS) biopsies will be taken according to our present routine protocol; simultaneously from these four transplant/organ sources at predestined points of time:

- Pancreas transplant (*P*)

- Kidney transplant (*K*)

- Duodenal segment of pancreas transplant (*tD*)

- Duodenum of recipient = native Duodenum (*nD*) – Serves as ‘control’

• Baseline (Day 0; at Tx): *K +tD + nD* - These will be taken during surgery

• 3 weeks post-Tx: *P +tD + nD* - Endoscopic

• 6 weeks post-Tx: *P + K + tD + nD* - Endoscopic (P/tD/nD) + Percutaneous (K)

• 12 months post-Tx: *P + K + tD + nD* - Endoscopic (P/tD/nD) + Percutaneous (K)

Within the study, we also want to take conventional percutaneous, ultrasound-guided P biopsies at 6 weeks and 12 months post-Tx – in order to compare the yield (and complications) by EUS vs percutaneous P biopsies.

In addition, indication biopsies will be taken whenever there is suspicion of rejection

in either organ. Preferably, simultaneous P + tD + nD endoscopic biopsies, P

percutaneous biopsies and K percutaneous biopsies should be obtained.

All biopsies will be examined at our local pathology unit; the pancreas and duodenal biopsies by prof. [name] and dr. [name]; the kidney biopsies by prof. [name] and dr. [name]. The pancreas and kidney biopsies will be evaluated by well-known BANFF criteria, while duodenal biopsies will be rated according to Wu et al. (27).

- Histological evaluation of the scheduled and indication biopsies will involve comparisons between biopsies from the various transplants/organs of the same patient.
  - Rejection histology scores.
  - Immunoshistochemistry on immunologic markers (CD25, FOXP3, CD4, CD3, CD8, CD45RO, perforin, granzyme A/B, etc).
    - Blood samples will be obtained at the time of transplantation and the later scheduled appointments indicated above.
  - Study of immune cell activation (CD25, FOXP3, CD4, CD3, CD8, CD45RO, perforin, granzyme A/B, etc) and cytokines (IL-2, TNF-a, IFN-g, IL-10, IL-12 etc).
  - Compare biomarkers in serum, indicative of acute rejection, by at least weekly blood sampling post-Tx (RNA microarray on a series of genes related to rejection, quantitative PCR on selected genes) (28-29).
  - Study of donor specific antigens (DSA)
    - DSA present pre-Tx (already routine)
    - The evolution of de novo DSA (dnDSA), with samples taken at 6 weeks, 12 months (concurrent with scheduled biopsies) and 24 months post-Tx – as well as when indication biopsies are performed.

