**1 INTRODUCTION AND BACKGROUND**

The first pancreas transplantation (PTx) was performed in Minnesota in 1966 by Kelly

and colleagues (1). In recent years the number of procedures has grown considerably worldwide, and is now a well-established treatment option for patients with diabetes mellitus with and without concomitant diabetic End-Stage Renal Disease (ESRD) (2-4). The indication for PTx is advanced and/or badly controlleddiabetes mellitus (”brittle” diabetes, severe hypoglycemic episodes,”unawareness”, etc). Solitary pancreas transplantation (SPT; without concomitant kidney transplantation) is usually classified as PTx alone (PTA), PTx after kidney transplantation (PAK) or PTx after islet transplantation (PAI). Kidney transplantation of the diabetic uremic population increases survival compared to long-term dialysis (5, 6). Transplant options for patients with diabetic end-stage nephropathy include simultaneous pancreas-kidney (SPK), live donor kidney (LDK) and deceased donor kidney (DDK) transplantation. SPK transplantation relieves not only the patient’s uremia, but also alleviates the hyperglycemic state of diabetes. Large international patient registries show that patient survival rates after SPK have reached more than 95% at 1 year and 87% at 5 years post-transplant, respectively (2). Nevertheless, PTx as treatment for type 1 diabetes has not gained the same popularity as transplantation of other organs, partly because PTx have been associated with a high rate of surgical complications; particularly bleeding, thrombosis and exocrine leakage. Furthermore, there has been a lack of reliable, non-invasive rejection monitoring instruments, and the invasive, percutaneous pancreas biopsies have traditionally been associated with a high rate of complications (exocrine leakage, bleeding).

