| PA Chest X-ray | **X** | To be obtained when clinically indicated | | | | | | | | |
| Complete blood count | **X** | **X** | **X** | **X** | **X** | **X** | **X** | **X** | | **X** |
| Fasting Blood Chemistries incl. amylase, lipase, CRP | **X** | **3 days a week** | | | **X** | **X** | **X** | **X** | | **X** |
| Blood T-cell counts | **Daily** | | |  |  |  |  |  | |  |
| Blood C-peptide, HbA1c, Auto-Ab | **3 days a week** | | | | **X** | **X** | **X** | **X** | | **X** |
| Microdialysis monitoring w/ catheters | **X** | | |  |  |  |  |  | |  |
| Blood fasting total, LDL and HDL-cholesterol and triglycerides | **X** | **X** | **X** | **X** | **X** | **X** | **X** | **X** | | **X** |
| Scheduled endoscopic (EUS) biopsies | **tD + nD** |  |  | **P + tD + nD** | **P + tD+nD** |  |  |  | | **P + tD+nD** |
| Conventional percutaneous US-guided biopsies | **K** |  |  |  | **P + K** |  |  |  | | **P + K (12)** |
| Blood immunology: RNA arrays.  Quantitative RT-PCR | **X** | **X** | **X** | **X** | **X** | **X** | **X** | **X** | | **X(12+24)** |
| HLA Donor specific antigens (DSA) | **X** |  |  |  | **X** |  |  |  | | **X (12+24)** |
| CMV-PCR | **X** |  |  | **X** |  |  | **X** | **X** | | **X** |
| Pregnancy Test | **X** | Whenever clinically indicated | | | | | | | | |
| Concomitant Medication | **X** | **X** | **X** | **X** | **X** | **X** | **X** | **X** | | **X** |
| Tacrolimus Trough Levels |  | **Week 1** | **Week2+ 3** | **X** | **X** | **X** | **X** | **X** | | **X** |
| MMF Through Levels | **X** | **X** | **X** | **X** | **X** | **X** | **X** | **X** | | X |
| Adverse Event Monitoring |  | **X** | **X** | **X** | **X** | **X** | **X** | **X** | | **X** |

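### The schedule does not support comparing complications of EUS and percutaneous pancreas biopsies: every scheduled percutaneous biopsy shares its time point and graft with an EUS biopsy, and there is no spacing or attribution rule

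*Protocol*

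**What the plan says.** Section 2.3 schedules pancreas (P) biopsies by the endoscopic route at three time points:

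- The first is by endoscopy alone: "3 weeks post-Tx: *P +tD + nD* - Endoscopic"
- The second brings in the kidney, sampled through the skin: "6 weeks post-Tx: *P + K + tD + nD* - Endoscopic (P/tD/nD) + Percutaneous (K"
- The third repeats that pattern a good while later: "12 months post-Tx: *P + K + tD + nD* - Endoscopic (P/tD/nD) + Percutaneous (K"

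It then adds the second route: "Within the study, we also want to take conventional percutaneous, ultrasound-guided P biopsies at 6 weeks and 12 months post-Tx", and gives the purpose: "in order to compare the yield (and complications) by EUS vs percutaneous P biopsies".

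The flow chart in Section 15 agrees. Its row "Conventional percutaneous US-guided biopsies" lists P and K at week 6 and at month 12, in columns where the endoscopic row also lists P. In the week 3 column only the endoscopic row has an entry.

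For indication biopsies, Section 2.3 asks for both routes together where possible: "Preferably, simultaneous P + tD + nD endoscopic biopsies, P", continuing with percutaneous pancreas and kidney samples.

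Section 9 requires the onset date, nature and outcome of every adverse event. The causality scale in Section 9.1 is written for drugs, and treatment is defined there as the agents given. It has no category for a procedure or a biopsy route.

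**The concern.** Yield and complications behave differently in a paired design. Each route produces its own specimen, so adequacy and diagnosis can be compared within the patient. A leak, bleed or pancreatitis belongs to the graft, and at 6 weeks and 12 months that graft has been punctured by both routes.

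The relative safety of the routes is an open question in this protocol. The introduction recalls that "percutaneous pancreas biopsies have traditionally been associated with a high rate of complications (exocrine leakage, bleeding", whereas Section 1.1 reports no complications in 18 recent percutaneous biopsies. EUS-guided biopsy is also part of the study rationale in Section 2. A published comparison of complications by route could influence which route other centres prefer. Here it would rest on case-by-case judgement under no stated rule, and Section 2.7 notes that the researchers also treat the patients.

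**Working it through.** The protocol gives no rate, sample size or power for this comparison, so there is no figure to reproduce. The check is of the schedule, followed by an illustration.

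**Step 1. Routes by scheduled time point (Section 2.3; Section 15 for week 6 and month 12)**

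| Time point | EUS P | Percutaneous P | Percutaneous K (kidney graft only) |
|---|---|---|---|
| Week 3 | yes | no | no |
| Week 6 | yes | yes | yes |
| Month 12 | yes | yes | yes |

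The flow chart puts the later endoscopic entry in a combined column for months 12, 24, 36 and 60. I follow Section 2.3, which names 12 months only. Either reading leaves no time point with percutaneous P alone.

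**Step 2. Number of occasions**, with 60-80 patients (Section 5), assuming that every patient keeps the graft and has every biopsy:

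- both routes: 2 × 60 = 120 to 2 × 80 = 160
- EUS alone (week 3): 60 to 80, one third of the scheduled EUS pancreas biopsies
- percutaneous alone: 0

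**Step 3. What a shared occasion shows.** Let pE and pP be the complication risks of the EUS and percutaneous biopsy, taken as independent. Without attribution, only the risk of any event is observed:

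P(any) = 1 − (1 − pE)(1 − pP)

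The documents give no rates by route for this study, so those below are assumed, over 1% to 5%.

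| pE | pP | P(any) | Expected events in 120 / 160 |
|---|---|---|---|
| 1% | 3% | 1 − 0.99 × 0.97 = 3.97% | 4.8 / 6.4 |
| 3% | 1% | 1 − 0.97 × 0.99 = 3.97% | 4.8 / 6.4 |
| 1% | 5% | 1 − 0.99 × 0.95 = 5.95% | 7.1 / 9.5 |
| 5% | 1% | 1 − 0.95 × 0.99 = 5.95% | 7.1 / 9.5 |

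The formula is symmetric in pE and pP. The event count cannot show which route carries the higher risk.

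**Step 4. Can week 3 supply the missing piece?** One could take pE from week 3 and solve for pP. This assumes that EUS risk is the same at week 3, week 6 and month 12, and that the kidney biopsy adds nothing. It is also imprecise. At assumed EUS rates of 1-5%, week 3 yields 60 × 0.01 = 0.6 to 80 × 0.05 = 4.0 expected events. With no events, the upper limit of the two-sided 95% interval is 1 − 0.025^(1/60) = 6.0% or 1 − 0.025^(1/80) = 4.5%. Both exceed 3.97%. If 3.97% were observed on shared occasions, pP could then be anything from 0 to 3.97%, even ignoring sampling error in the 3.97%.

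**Step 5. The one documented rate.** For 0 of 18 percutaneous biopsies (Section 1.1), the upper 95% limit is 1 − 0.025^(1/18) = 18.5%. This neither supports nor excludes any rate used above.

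**The case against.** Several objections are sound and limit the point.

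- **Same time point, not same session.** The protocol fixes nominal time points for the added percutaneous biopsy, not a day or order. If the routes fall on different days, onset dates may separate some events, and others could be localised clinically. A reader might infer that no event can ever be assigned; the documents do not support that. What stands is that nothing requires a separation or says how to judge one. The general wording leans towards simultaneous sampling, including the remark in Section 10.2 on the simultaneous biopsy strategy.
- **Not every EUS biopsy is affected.** Week 3 is EUS alone, so an event then belongs to the endoscopic session, which also samples both duodenal sites. It has no percutaneous counterpart.
- **The kidney biopsy is not universal.** Recipients without a simultaneous kidney are eligible, and Section 1.1 puts solitary pancreas transplants at about 10% of past activity.
- **Counting rules may sit in an analysis plan.** A reader might infer that each event will be counted against both routes, forcing the difference to zero. The protocol has no such rule. A later plan could add attribution criteria, but it could not create percutaneous-only exposure, which the schedule excludes.
- **The aim is ancillary.** It is not among the objectives in Sections 2.1 and 2.2, Section 10.3 names no test for it, and the stopping criteria in Section 10.4 do not use it. This stands in full.

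**Conclusion.** The point holds in limited form. At the only two scheduled percutaneous time points both routes are used on one graft, with no spacing, order or attribution rule. Complications there cannot be reliably assigned to a route, and the schedule does not support the complication half of the comparison in Section 2.3. Up to 120-160 shared occasions are affected, against none with percutaneous biopsy alone.

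The counts assume full attendance and surviving grafts. The rates in the working are assumed and show only that opposite truths give the same data. They do not estimate bias, and the documents do not indicate which route is riskier.

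A reader might extend the problem to the primary endpoint of surgical complications. That does not follow: the endpoint counts patients with a complication involving reoperation or reintervention, without regard to biopsy route. The paired comparison of yield is also sound.

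**What to change.** Change the wording of Sections 2.3 and 10.3 and leave the biopsies as they are.

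1. Keep the paired EUS versus percutaneous comparison for yield only, and drop the head-to-head comparison of complications.
2. Report complications descriptively per biopsy session, meaning all biopsies at one scheduled time point, with 95% confidence intervals. Show EUS-only sessions (week 3) and combined sessions (week 6 and month 12). Giving week 6 and month 12 separately lets each patient count once per interval.
3. For each event, give the date of onset relative to each puncture.
4. State that a difference between session types also reflects time since transplantation, repeat puncture and, in recipients with a kidney graft, the kidney biopsy. It is not an estimate of percutaneous risk.

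The cost is wording, plus recording the date of each puncture beside the onset dates that Section 9 already requires. The downside is that the study cannot claim a complication rate specific to percutaneous biopsy, and the session-level figures will be sparse.
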